#### Smoking Topography

Behavioral adaptations were measured by ST, including puff number per cigarette, average puff duration (seconds), average interpuff interval (seconds), average flow rate (mL/s), and average and total volume (mL) [14]. We used the portable CReSS device to measure topography over five, daily, 8-hour periods per week: at baseline (Week 1), during the initial switch (Weeks 2 and 3), at postwashout baseline (Week 7), and again after the crossover switch (Weeks 8 and 9). Participants were trained in the use of the device by the study team at the initial lab visit in a specialized facility designed with proper ventilation to accommodate indoor smoking research. Multiple days of measurement allowed for assessment of reliability and sensitivity of topography changes as a function of the filtered and unfiltered cigarette switch. Topographic measures by CReSS have been compared to direct observation via video recordings [15]. One limitation of the CReSS device is inconsistent methodology and guidelines in calibration settings and standard usage, as well as established acceptable ranges of ST variables (eg, peak flow rates, interpuff interval, etc). However, past studies have mainly used manufacturer guidelines with added modifications and/or adaptations [31], and these were recommended in a recent review [32]; there are no changes in recommendations for newer devices.

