### Sample Size

The study sample size is 40 participants, sufficient to detect moderate within-subject effect sizes (*f*=0.35) with a moderate correlation between repeated measures (*r*>0.50). This two-by-two crossover design has statistical power of 80% for a sample size of 20 in each group to detect an effect size of 10% change in average number of cigarettes smoked per day. We tried to recruit at least 10 participants of non-White ethnicities. If participants prematurely discontinued from the trial prior to crossover, we attempted to recruit replacements from the eligible pool or advertise for new participants. We recruited 20 women out of the 40 participants and randomized by sex. Sex stratification is of interest because men and women may metabolize smoke differently due to differences in body size and differences in cigarette preference and behavior. Any woman who becomes pregnant during the trial will be excluded from further participation [38].

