### Statistical Methods

#### Primary and Secondary Outcomes

Descriptive statistics will be used to analyze baseline data to assess any imbalances between groups in baseline demographics and prerandomization characteristics. Stratified analyses and analyses of covariance will be performed to control for any baseline imbalances. To account for the crossover design and repeated measures, linear mixed-effects models with fixed effects for period and exposure sequence (ie, filtered then unfiltered or unfiltered then filtered) and with random effects for sex and participant will be used to analyze continuous outcomes and changes from baseline. Log transformation of nonnormal continuous measures will be performed when necessary. If data do not fit a linear model, generalized models will be considered. Model variance will be fit using a compound symmetry correlation structure with default degrees of freedom, which assumes constant variance between periods, with alternative covariance structures explored in the event of nonconvergence. For analysis of ordinal questionnaire data, we will assess for exposure and period effects using ordinal repeated-measures models with fixed effects for exposure sequence and period and with random effects for sex and participant. Prespecified cutoffs and thresholds for biomarkers and topography variables will be chosen based on a comprehensive literature review prior to conducting any analysis. Normalization and sensitivity analysis will be performed, if required. Changes in means for each continuous measure between participants and between weeks within treatment conditions will be calculated. Mean differences between exposure arms for these continuous measures will also be compared. *P* values and 95% confidence intervals will be reported when providing results from fitted models. All analyses will be performed using SAS 9.4 (SAS Institute) [41]. Noncomplier and dropout data will be utilized in mixed methods models up to the point of dropout and noncompliance for an intent-to-treat analysis. A completer-only (ie, per-protocol) analysis will also be run as a secondary analysis.

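### If weekly or daily records enter the exposure model, participant-only compound symmetry can make confidence intervals for the filtered–unfiltered contrast too narrow

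*Protocol article*

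**What the plan says.** The Protocol article (Statistical Methods, Primary and Secondary Outcomes) plans linear mixed models for continuous outcomes and for changes from baseline, intended to handle both the crossover and the repeated measurements. Period and sequence are the listed fixed effects; sex and participant are the listed random effects. On covariance it says: "Model variance will be fit using a compound symmetry correlation structure with default degrees of freedom, which assumes constant variance between periods". The only occasion it gives for departing from that structure follows in the same sentence: "with alternative covariance structures explored in the event of nonconvergence". No participant-by-period term is named. The same section also plans comparisons of weeks within a condition.

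Measurement frequency differs by outcome:

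- **Topography** (Smoking Topography): the device is used to "measure topography over five, daily, 8-hour periods per week", in both weeks of each condition.
- **Cigarettes per day, expired CO and some scales** (outcome sections): recorded weekly or at each visit.
- **Urine biomarkers** (Plans for Assessment and Collection of Outcomes): Weeks 1, 3, 7 and 9, so one sample after the switch in each period.
- **Knowledge and attitude items, the Fagerström test and the Brief Wisconsin Inventory**: enrollment and final visit only.

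**The concern.** A participant switches exposure once, between periods. Extra weeks or days within a period make that period's mean more precise, but they are not new replicates of the switch. A model with only a participant effect, which is what compound symmetry by participant amounts to, treats all of a participant's records as independent given the participant. Weeks 2 and 3 are then allowed no more correlation than Weeks 2 and 8, which lie six weeks apart with a washout between them.

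If a participant's level drifts between periods, or participants differ in their response to unfiltered cigarettes, records in the same period share a deviation that this model cannot represent. The deviation is diluted into a pooled residual made up mostly of week-to-week or day-to-day noise, and that residual becomes the error term for the exposure contrast. Smoking behaviour and CO findings could then be declared on intervals that are too short, and this pilot is meant to inform both legislation and a larger trial.

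The stated safeguard would not catch this. Compound symmetry is among the simplest structures and seldom fails to converge, and a misfit is not nonconvergence.

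**Working it through.** **The plan's own figures.** The article gives no type I error or variance component to reproduce. Its claim of "statistical power of 80% for a sample size of 20 in each group", for a shift of one tenth in daily consumption, comes without an SD or an alpha and cannot be checked. With two-sided 5% and 38 df it needs a standardised paired difference of 0.455, so an SD of the within-participant difference of 10/0.455 ≈ 22% of mean consumption. That figure does not enter the check below.

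**Inputs from the article.** 37 participants enrolled (40 planned); two periods; k = 2 weekly records per period, or k = 5 × 2 = 10 daily topography records.

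**Assumptions.** Two-sided 5%, inferred from "95% confidence intervals will be reported when providing results from fitted models". An exposure term is in the model. Participant-by-period variance t is 0.2, 0.5 or 1 times the residual variance s; the article gives no value.

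**Formula.** On the scale of one record, the correct error variance for the exposure contrast is kt + s. The participant-only model instead pools it with the within-period residual. Per participant there is about 1 df of the former and 2(k − 1) of the latter, so the assumed variance is [(kt + s) + 2(k − 1)s]/(2k − 1). The ratio of true to assumed variance is

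R = (kt + s) / {[(kt + s) + 2(k − 1)s]/(2k − 1)}.

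The model's standard error is 1/√R of the true one, and type I error is about 2[1 − Φ(1.96/√R)].

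Examples with t/s = 1:

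- k = 2: 3 / [(3 + 2)/3] = 1.80
- k = 10: 11 / [(11 + 18)/19] = 7.21

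| k | t/s | R | model SE / true SE | type I, formula | type I, simulated |
|---|---|---|---|---|---|
| 2 | 0.2 | 1.24 | 0.90 | 8% | 8.2% |
| 2 | 0.5 | 1.50 | 0.82 | 11% | 9.9% |
| 2 | 1 | 1.80 | 0.75 | 14% | 14.2% |
| 10 | 0.2 | 2.71 | 0.61 | 23% | 24.5% |
| 10 | 0.5 | 4.75 | 0.46 | 37% | 38.0% |
| 10 | 1 | 7.21 | 0.37 | 47% | 46.9% |

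The simulation used 37 participants, no true effect and 4,000 trials per setting (standard error about 0.4 to 0.8 percentage points). With t = 0 it gave 4.8%. A second simulation with 40 participants and 20,000 trials gave 14.7% (k = 2) and 46.6% (k = 10) at t/s = 1.

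**One record per period.** Type I error was 4.7–5.3% throughout. Analysing period means gave 4.7–5.4% in every setting.

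**Change from the period's own baseline.** Subtracting one baseline value from every record in a period adds a shared deviation even when t = 0. One baseline week has variance s, so it acts like t/s = 1 with k = 2, giving about 14% (simulated 14.5%). A mean of five baseline days has variance s/5, so it acts like t/s = 0.2 with k = 10, giving about 23% (simulated 23.5%).

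**Degrees of freedom.** With 40 participants the residual df are 38 + 80 = 118 (weekly) or 38 + 720 = 758 (daily). Using 38 df with the same standard error, when t is 30% of t + s, only moves type I error from 10.7% to 10.0% (weekly) and from 34.5% to 32.8% (daily). The missing variance component causes nearly all the inflation.

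**The case against.** The strongest reply is that the article never says weekly or daily records enter the exposure model. No week or day term is listed, the covariance sentence speaks of variance between periods, and most topography variables are defined as averages. If each period contributes one value, compound symmetry is valid and nothing is inflated. The aggregation level may also be settled in an analysis plan that is not shown. This stands, and it makes the point conditional. It does not remove it: the article does state the random effects, the covariance structure and the only trigger for changing it; it says the models are to handle repeated measures; and it mentions no averaging to period means.

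A second reply is that the participant-by-period variance is assumed. That also stands, and the range is shown for that reason. Some such variance is plausible: the periods are weeks apart, individuals may respond differently to losing the filter, and study cigarettes are supplied according to consumption in the week before. For changes from a period-specific baseline, no such assumption is needed.

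A reader might infer that the trial's intervals are certainly too narrow, that 24–47% is its expected error rate, or that the default degrees of freedom are to blame. The documents support none of these: the record level and the variance are not given, and the df effect is small. Nor are all questionnaires involved, since several are given only at enrollment and the final visit.

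**Conclusion.** The concern holds in conditional form. If two weekly records per period are modelled as stated, type I error is about 8–14% for t/s between 0.2 and 1. If ten daily topography records per period are modelled, it is about 24–47%. Both ranges rest on the assumed variance ratio, on several records per period entering the model, and on an exposure term that the linear-model sentence does not list by name. With one record per period the error rate is nominal. With t = 0 it is also nominal, except for changes from each period's own baseline.

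The outcomes at risk are cigarettes per day, CO, scales given at each visit, and topography. Urine biomarkers with one post-switch sample per period are not affected. For cotinine this relies on the four-week sampling schedule; the Cotinine section instead describes measurement at every visit, and the two should be reconciled.

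**What to change.** State, for each outcome, which records enter the exposure model. Then do one of the following:

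1. Analyse one mean per participant per period (or one mean change, where a period baseline is used).
2. Where weekly or daily records are modelled, add a random participant-by-period effect, with Kenward-Roger or Satterthwaite degrees of freedom so that the contrast is tested on roughly the number of participants rather than the number of records.

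Replace the nonconvergence trigger with a rule that does not depend on it alone, for example by fixing the participant-by-period structure in advance.

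The change is about one line of SAS code. The price is wider intervals: where t is positive, by the factor √R (1.34 for k = 2 and 2.68 for k = 10 at t/s = 1), which is the width the data warrant. If t is in fact zero and the outcome is not such a change score, period means with 38 df cost at most about 3% in width (2.024/1.960 = 1.033).

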#### Cigarettes Per Day: Self-Report and Butt Count

Standard survey questions measured how many days in the past month (enrollment [ie, baseline] visit), past week (weekly visits), and past 2 months (final visit) participants have smoked, as well as how many CPD they have smoked on those days (all study visits). In addition, participants returned their cigarette butts in a sandwich-size Ziploc bag or glass jar each week to provide a validation of their self-report. While these butts were disposed of as toxic waste in approved containers, a small portion were retained for future analyses. Previous studies have included butt counts with reliability set at 75% of returns [30]. We excluded butt count data from participants who did not return 75% of butts and provided incentive payments for returning cigarette butts at this level.

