### Plans for Assessment and Collection of Outcomes

There were eight scheduled lab visits, each with an incentive for attendance (see Participant Retention and Complete Follow-Up section). As shown in Table S1 in Multimedia Appendix 2, these visits were to occur weekly at baseline (Week 1), during the first 2 weeks of cigarette use (Weeks 2 and 3), during the postwashout baseline (Week 7), and during the second 2 weeks of cigarette use (Weeks 8 and 9). During each visit, participants were tested for expired CO, had blood pressure and weight measurements performed, and completed surveys (see Table S1 in Multimedia Appendix 2). At Weeks 1, 3, 7, and 9, participants provided a urine sample to measure normalized cotinine and carcinogen biomarkers. All collected urine samples were stored in a –80 °C freezer. Specimens were transported from Institution B to Institution A for laboratory testing.

During visits 2-4 and 6-8, participants visited the Institution B smoking laboratory facility with their topography device, cigarette butts, and unused cigarettes (left only on Weeks 3, 4, 7, and 8). Data from the topography device were downloaded so that the number of cigarettes logged in as smoked on the CReSS device could be compared to the total number of cigarettes or butts returned, as well as the number self-reported cigarettes smoked per day. Those deemed compliant with study procedures were paid for their time and supplied with another weeks’ supply of condition-assigned cigarettes. During visit 8, the same procedure was to be followed, except that it would be the final visit and no additional study cigarettes would be provided. Due to the COVID-19 pandemic, some of these procedures were curtailed and moved to remote follow-up.

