#### Missing Data

Missing data were to be minimized or avoided through extensive training of clinical research staff and repeated efforts to contact trial participants to obtain protocol-specified data. In the event of missing data, sensitivity analyses will be performed, including a completer analysis and multiple imputation approaches.

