#### Protections Against Risk

We measured biomarkers of carcinogen and nicotine exposures in order to assess the potential for long-term risk differences for unfiltered-cigarette versus filtered-cigarette smoking. In addition, because secondhand smoke is considered a risk exposure, and because this exposure is due to a combination of expired and side-stream smoke, this exposure to participants or their close contacts should be unaffected by the presence or absence of a filter.

We only recruited current smokers for this study, all of whom were also informed about the health consequences of smoking in the consent procedures. We trained study staff to be nonjudgmental toward smokers, to reassure them of anonymity in reporting findings, to reinforce the scientific value of this study, and to provide feedback after completion of the study. Both excluded individuals following the screening process as well as trial participants were referred for smoking cessation support to the state smoking cessation helpline. Any individuals deemed to have become ineligible, or those, for example, seeking to quit smoking, were provided with referrals and allowed to discontinue the trial.

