## Discussion

This project will provide preliminary scientific evidence of the individual consequences of removing filtered cigarettes from the commercial tobacco market and how larger clinical trials of switching to unfiltered cigarettes may be undertaken. Outcomes and changes due to smoking unfiltered cigarettes include smokers’ satisfaction, attitudinal changes, changes in ST, changes in the number of cigarettes smoked per day, changes in exhaled CO, and changes in urinary cotinine and tobacco carcinogens. This is critical information that may be needed to inform and advance state or local legislation to ban the sales of filtered cigarettes. Such legislation would reduce the environmental impact of nonbiodegradable cigarette butt waste due to the cellulose acetate filter, although there might still be some environmental contamination from butt remnants. It is unknown whether eliminating filtered cigarettes from the tobacco product market will change smoking behavior, such that smokers will be more likely to quit or reduce cigarette consumption. Given that filters are essentially a marketing tool and not a health protective device, cigarette marketing success is likely to be reduced without this tool. If unfiltered cigarettes are less palatable than filtered cigarettes, it is likely that fewer cigarettes will be smoked and fewer children will become addicted. This study will provide missing information as to how smokers might react to no longer being able to smoke filtered cigarettes. If information about the lack of health protection of filters and their environmental impact becomes more widespread, fewer smokers may choose to smoke filtered cigarettes. The preliminary findings this study could be addressed in larger clinical trials in order to have a more substantial impact on tobacco product regulatory science more generally.

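### The analysis labelled intent-to-treat stops using noncompliers' data at noncompliance, so it is an on-treatment analysis that can select on response

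*Protocol article*

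**What the plan says.** In Statistical Methods (Primary and Secondary Outcomes), the article fixes the main analysis set in one sentence: "Noncomplier and dropout data will be utilized in mixed methods models up to the point of dropout and noncompliance for an intent-to-treat analysis". It then adds: "A completer-only (ie, per-protocol) analysis will also be run as a secondary analysis". The Missing Data section says that, if data are missing, "sensitivity analyses will be performed, including a completer analysis and multiple imputation approaches". It also plans repeated attempts to reach participants for protocol-specified data.

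The article does not define noncompliance. The nearest text is in Plans for Assessment and Collection of Outcomes: "Those deemed compliant with study procedures were paid for their time and supplied with another" week's supply of the assigned cigarettes.

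Three other statements bear on the point:
- Protections Against Risk says that people who became ineligible, or "those, for example, seeking to quit smoking, were provided with referrals and allowed to discontinue the trial".
- Sample Size says: "If participants prematurely discontinued from the trial prior to crossover, we attempted to recruit replacements from the eligible pool".
- The Discussion says: "It is unknown whether eliminating filtered cigarettes from the tobacco product market will change smoking behavior", and it names quitting and smoking less as the possible changes.

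**The concern.** Intent-to-treat means that participants are analysed under the condition they were assigned, with the outcomes they had, whether or not they complied. A rule that stops using a person's data once they fail to comply answers a different question: what happens while people go along with the product.

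That difference matters here. Study Objectives asks what switching to unfiltered cigarettes does to smoking behavior and exposure. A smoker who rejects the unfiltered product, cuts down sharply or stops is showing part of that effect. If such behavior counts as noncompliance, the main estimate leaves out the responses of the people who reacted most. The results are meant to inform legislation and the design of a larger trial, and readers would take a figure labelled intent-to-treat as free of this selection.

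**Working it through.** **1. What the rule removes.** The measured weeks are 1, 2, 3, 7, 8 and 9 (Intervention Description).
- *Dropout:* nothing is observed afterwards, so using data up to that point is unavoidable.
- *Noncompliance:* observation need not end. CPD, expired carbon monoxide and survey measures are scheduled at every visit. Using data only up to noncompliance discards what those visits record.
- *Literal reading in the crossover:* noncompliance in Week 2 or 3 removes everything later, including Weeks 7 to 9. For someone assigned unfiltered cigarettes first, that deletes their filtered comparison period.

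**2. The plan's own yardstick.** Sample Size gives 80% power, with 20 per group, for a 10% change in CPD. No standard deviation is stated, so the 80% cannot be reproduced. With two-sided alpha of 0.05 (assumed) and 38 degrees of freedom, 80% power at N = 40 needs a standardized difference of 0.4546. That implies a within-person standard deviation of the difference of 10 / 0.4546 = 22.0% of the mean. The point does not depend on this; the 10% serves only as a scale.

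**3. Illustration by arithmetic.** All rates are assumed. A share p is noncompliant on unfiltered cigarettes with CPD change d1 = -30%; the rest have d0 = -5%.

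Full effect = (1 - p) × d0 + p × d1. If noncompliers contribute no unfiltered data, the truncated estimate is about d0.

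| p | Full effect | Truncated | Gap = p × (d0 - d1) |
|---|---|---|---|
| 10% | 0.9 × (-5) + 0.1 × (-30) = -7.5% | -5% | 2.5 points |
| 20% | 0.8 × (-5) + 0.2 × (-30) = -10.0% | -5% | 5.0 points |
| 30% | 0.7 × (-5) + 0.3 × (-30) = -12.5% | -5% | 7.5 points |

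The sign of the gap follows d0 - d1. If noncompliers changed less than the others, truncation would overstate the fall in CPD instead.

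**4. When some unfiltered data survive.** The -5% is the extreme case, because the rule keeps data until the event. A simulation covers a partial case: 1,500 trials per scenario, N = 40, six measured weeks, and a compound-symmetry model with variance components held at their true values (correlation 0.5, total SD 22.6% of the mean). A share q halves CPD in the first unfiltered week and smokes nothing in the second; everyone else is unchanged. In the all-data analysis the zeros are recorded, and those given unfiltered cigarettes first smoke at their usual level in the second period. The truncated analysis keeps the halved week and nothing later.

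| q | All data | Truncated | Share lost |
|---|---|---|---|
| 5% | -3.9% | -1.2% | 1 - 1.2/3.9 = 69% |
| 10% | -7.4% | -2.4% | 1 - 2.4/7.4 = 68% |
| 15% | -11.2% | -3.8% | 1 - 3.8/11.2 = 66% |
| 20% | -14.7% | -4.8% | 1 - 4.8/14.7 = 67% |

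Hand check of the all-data column: these participants average (-50 - 100)/2 = -75%, and q × (-75%) gives -3.75%, -7.5%, -11.25% and -15%, close to the simulated values.

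**5. Whether another planned analysis repairs it.** The completer-only analysis keeps those who finished, so it shares the selection. Multiple imputation is a sensitivity analysis for missing data. Values that were observed and then set aside are not missing, and under a missing-at-random model imputation would not be expected to return the zeros of people who stopped smoking.

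**The case against.** The strongest reply is that this is a pilot with one loosely worded sentence. Where the article speaks of compliance or adherence, it means study procedures (device use, butt return, visits), which apply in both conditions, and imputation and follow-up efforts are planned. Much of this stands. The article does not say that noncompliance means returning to filtered cigarettes, and every rate above is assumed. The reply does not rescue the label: whatever noncompliance means, observed data after it are set aside.

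A reader might infer more than the text supports:
- *That noncompliance falls almost only in the unfiltered condition.* This is plausible, since everyone already smokes a filtered version of the brand, but it is not stated.
- *That quitters leave with no CPD recorded, or that replaced participants vanish from the analysis.* The text allows people seeking to quit to leave, uses data up to dropout, and seeks replacements for any discontinuation before crossover. It nowhere removes the replaced person's data.
- *That no unselected result remains.* Multiple imputation is planned, and its assumptions may be set elsewhere.
- *That the 75% butt rule creates a false fall in CPD.* The text is "We excluded butt count data from participants who did not return 75% of butts"; self-reported CPD is untouched. Assume mean returns of 90% and 80%, an SD of 8 points and no true change. The butt count then shows 80/90 - 1 = -11.1% without the rule and about -7.7% with it, so the rule shrinks that artefact.

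**Conclusion.** The sentence is wrong as written. It describes an on-treatment analysis and calls it intent-to-treat, and no other planned analysis restores the observed values it drops. Because rejecting the product, cutting down and quitting are responses under study, the cut can bias the estimated effect of switching.

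Size and direction cannot be settled from the article. Under the assumed 10 to 30% noncompliance in step 3, the gap is at most 2.5 to 7.5 percentage points of CPD, against a design effect of 10%. It would be smaller where noncompliers contribute some unfiltered weeks, absent where they respond like everyone else, and reversed where they change less. The finding concerns the analysis rule and its label. It does not question participants' freedom to leave, and it does not extend to the butt-count rule.

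**What to change.** - Define the main analysis as all randomized participants, including any who discontinued and were replaced, with all observed data under the assigned condition regardless of compliance.
- Use a CPD of 0 where stopping smoking is actually recorded; do not assume it for unobserved days.
- State what counts as noncompliance.
- Report discontinuation and quitting by condition.
- Rename the truncated analysis on-treatment and keep it secondary, beside the completer-only analysis.

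Cigarettes dispensed minus returned should not be adopted as a substitute count. Intervention Description limits study supplies to the four treatment weeks, so the measure does not exist for baseline weeks, and it misses participants' own cigarettes.

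The cost is a change of wording and one extra model run on data already held. Weeks of mixed product use may dilute the biomarker contrasts, which is a reason to show the on-treatment result alongside. Outcomes that were never collected after noncompliance cannot be recovered, and the report should say how many there are.
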